### Secondary outcome measures

The prevalence of DRPs in patients will be determined at baseline and after 6 months in both groups. The 6 month questionnaire will be similar to the screening questionnaire omitting questions that only need to be asked at the beginning of the study. An independent clinical pharmacologist and GP will assess the DRPs on the basis of the screening questionnaire and the pharmacist’s medication overview using the DOCUMENT checklist [48]. DOCUMENT stands for Drug selection, Over- or underdose prescribed, Compliance, Untreated indications, Monitoring, Education or information, Non-clinical and Toxicity or adverse reaction and has multiple subcategories.

Research suggests that greater treatment satisfaction is associated with better compliance [49]. Patient satisfaction about medication in general will be assessed by the single-item Medication Satisfaction Questionnaire (MSQ) “Overall, how satisfied or dissatisfied are you with your current medication?” with a written response assessed on a seven point Likert like scale at baseline, 3 and 6 months [50].

Medication adherence will be measured in two ways; 1. Check for at least one pharmacy delivery in the last six months for all chronically used medication and 2. Self-reported adherence as questioned in the screening and follow-up questionnaires at baseline and 6 months. Self-reported adherence is part of the developed screening questionnaire.

Costs will be measured from a societal perspective. To calculate the costs of the intervention, information will be recorded by the expert team, the GP, the pharmacist and the practice nurse in terms of time and material spent on performing the CMR and the monitoring of the patients. Healthcare costs made by the patient will be assessed from a societal perspective using an slightly adapted version of the Dutch Medical Consumption Questionnaire (*i*MTA) questionnaire on care consumption, including informal care after 3 months (t = 1) and after 6 months [51]. Information on prescribed medication will be derived from the pharmacy administration information system (PAIS). Lost productivity costs will not be included since almost all patients will be retired. Healthcare utilisation will be valued according to guidelines for economic evaluation in healthcare in the Netherlands [52].

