### Participants

Patients of 65 years and older are eligible if they newly present with a geriatric giant in general practice use at least one prescription drug chronically. A new geriatric giant is defined as being a first episode if the problem has not been noted in the patients’ medical file during the previous 12 months. Patients with geriatric giants are identified on the basis of the ICPC coded diagnoses [31] (see Additional file 1) in their electronic medical record. Chronic use of at least one drug is defined as at least three prescriptions in the last 12 months in the GP practice. In The Netherlands, prescriptions are always for a maximum of three months of treatment.

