### Outcome measures

Measurements by means of patient questionnaires and proxy assessments will be carried out at baseline, after 3 and 6 months It is expected that some patients will develop either cognitive problems or other difficulties precluding that they fill out the questionnaires adequately during the study. Self-assessment in these patients might therefore be less reliable or become not feasible. Proxy assessment could be a substitute for self-assessment of quality of life [38]. Therefore, patients will be asked to indicate two proxies: an informal care giver and a professional care giver who will fill out a proxy assessment questionnaire of the patient’s quality of life. Data on morbidity and laboratory test results will be collected using medical records in the GP practices. Characteristics of medication, changes in medication and adherence to medication will be assessed using dispensing data from the patient’s pharmacist. All outcomes will be assessed at patient level.

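### The pharmacy-based adherence check needs one delivery in six months, although a prescription covers at most three, so it cannot detect partial non-adherence

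*Protocol article*

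**What the plan says.** Under Secondary outcome measures, the protocol article states that "Medication adherence will be measured in two ways". The first is a "Check for at least one pharmacy delivery in the last six months for all chronically used medication". The second is "Self-reported adherence as questioned in the screening and follow-up questionnaires at baseline and 6 months". The Outcome measures section names the data source for the first: "changes in medication and adherence to medication will be assessed using dispensing data from the patient’s pharmacist".

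Two statements under Participants bear on the threshold. One limits the supply: "prescriptions are always for a maximum of three months of treatment". The other sets the eligibility standard for chronic use: "Chronic use of at least one drug is defined as at least three prescriptions in the last 12 months in the GP practice".

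Adherence is also a target of the intervention. The last step of the expert team's review covers adherence together with user and knowledge problems. The same review looks for overtreatment, and the patient's own GP then puts medication changes into effect. Under Monitoring the medication use, the researchers check at six months which drugs have changed relative to the review outcome and/or baseline use. The article does not link that check to the adherence score.

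**The concern.** The window is twice as long as the longest prescription, yet one delivery is enough to pass. The rule separates patients who collected nothing in six months from those who collected something. It does not separate a patient who collects on time from one who collects half as often as needed. If the review improves adherence mainly by turning irregular users into regular ones, the pharmacy measure would record no change, and a null result on it could not be interpreted.

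A second issue is what counts as chronically used medication at six months. The article does not say whether this is the baseline list or the list after the review, and it does not say how drugs stopped on advice are handled. Review-led stops occur only in the intervention arm, so this choice could affect the two arms differently.

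**Working it through.** The article states no adherence rate or coverage figure, so there is nothing to reproduce. The check uses its own rules.

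**Inputs**
- Window W = 6 months and pass threshold of one delivery (Secondary outcome measures).
- Longest prescription s = 3 months (Participants).
- Chronic use: at least 3 prescriptions in 12 months (Participants).
- Assumptions made here: one delivery dispenses at most one prescription, collection is regular at interval g, and delivery dates fall evenly relative to the start of the window.

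**Step 1: supply from one delivery.** Share = s/W = 3/6 = 50%. With a two-month prescription it is 2/6 = 33%, and with a one-month prescription 1/6 = 17%.

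**Step 2: who passes.** With a three-month supply every g months, long-run supply is the smaller of 1 and 3/g. The chance of at least one delivery in the window is the smaller of 1 and 6/g.
- g = 3: supplied 100%, pass 100%
- g = 4: supplied 75%, pass 100%
- g = 5: supplied 60%, pass 100%
- g = 6: supplied 50%, pass 100%
- g = 7: supplied 43%, pass 6/7 = 86%
- g = 9: supplied 33%, pass 6/9 = 67%

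The score does not vary at all between 50% and 100% supply, and most patients somewhat below 50% still pass.

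**Step 3: carry-over.** At g = 4 a six-month window holds 6/4 = 1.5 deliveries on average, so about half of such patients show only one. Each supply leaves a gap of one month, and the window can contain at most two such months, so their cover is at least 4/6 = 67%. A single delivery is therefore compatible with more than 50% cover. This limits what one delivery proves about a given patient. It does not change Step 2, where the half-supplied patient passes every time.

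**Step 4: comparison with the article's own standard.** One delivery per six months is two a year, at most 2 × 3 = 6 of 12 months (50%). The chronic-use definition asks for three prescriptions a year, up to 3 × 3 = 9 of 12 months (75%). The adherence rule is the looser of the two.

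**Step 5: stopped drugs, if the baseline list is used.** A fully adherent patient with three-monthly deliveries fails only if the drug is stopped before its first delivery in the window. For a stop at t months the chance is 1 − t/3:
- t = 0.5: 83%
- t = 1: 67%
- t = 1.5: 50%
- t = 2: 33%
- t = 3: 0%

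With monthly deliveries it happens only for stops within the first month. With the post-review list it is 0% throughout.

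**The case against.** The strongest reply is that the delivery check is only one of two measures. A coarse check can find drugs that are not collected at all, while self-report can address partial use, and the DOCUMENT classification of drug related problems also has a compliance category. This is fair, and it means the point concerns one measure and not the whole adherence conclusion. It does not remove the point: patients are not blinded to allocation, and the pharmacy record is the only objective adherence measure of the two.

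It can also be said that days covered is merely a finer metric and that such detail belongs in an analysis plan. That would hold if the article were silent, but it states the rule outright, and the rule sits badly with its own three-month limit. The carry-over argument stands as far as Step 3 takes it.

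A reader might go further and infer that the measure is biased against the intervention, or could reverse the sign of the adherence result, because the review stops drugs. The article does not support that. On the ordinary reading a stopped drug is no longer chronically used and drops out. Even with a baseline list, one delivery before the stop is enough to pass, and stops come only after data collection, expert review and a GP consultation. The article gives no stop rates or stop times, so no size can be put on such a bias. What stands is a conditional risk that the text leaves open.

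**Conclusion.** The concern holds as a statement about sensitivity. Given the three-month maximum, the pharmacy check scores a patient who collects a three-month supply every six months as adherent in every case. It gives the same score to regular supply anywhere from 50% to 100%. This rests on the two stated rules, on one prescription per delivery and on regular collection. It does not mean that everyone with a single delivery has only half the drug.

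Misclassification of stopped drugs is possible but not established. It needs a drug list fixed at baseline and a stop before the first delivery in the window, roughly within the first three months. If both applied it would fall mainly on the intervention arm.

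Adherence is a secondary outcome, so the conclusions on quality of life and geriatric symptoms are unaffected. The change is still worth making, because the outcome is named, the intervention targets it and the data are already being collected.

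**What to change.** From the pharmacy dispensing data, compute for each chronic drug the proportion of days covered over the six months, average it per patient, and analyse that as the pharmacy adherence outcome. If a binary version is wanted, use 80% or more; this cut-off is a proposal here and does not come from the article. State the reference drug list. Count days only while the drug is prescribed, so that counting ends at the prescriber's stop date. The six-month check of medication changes identifies the drugs concerned.

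Simply raising the threshold to two deliveries is not a good substitute. At 80% cover a three-month supply is collected every 3/0.8 = 3.75 months, which gives 6/3.75 = 1.6 deliveries per window. About 40% of such patients would show only one delivery and fail.

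The cost is some extra programming and the retrieval of stop dates. No new patient contact or questionnaire is needed.

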### Intervention

#### Preparatory steps

The research assistant prepares together with the practice nurse the CMRs for the expert teams (see below). The required information from the electronic medical files from the GP practice, the pharmacy and the screening questionnaire is collected. This information consists of the actual drug use of the patient including OTC drugs, drug delivery history, potential DRPs, the medical problems of the patient, laboratory test results, e.g. renal function and other measurements such as blood pressure.

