#### Monitoring the medication use

Six months after inclusion a check will be carried out by the researchers to identify medication changes compared to the outcome of the CMR (intervention group) and/or compared to baseline drug use of all participating patients. The patients’ GPs will receive a signal if new DRPs are identified. The follow-up of this signal is outside the scope of this study.

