#### Training

Expert teams will follow accredited online courses for medication reviews and pharmacology in elderly and two medication review workshops. Participating GPs and practice nurses of the intervention practices will be instructed how to carry out the study protocol and will receive a handbook.

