## Discussion

This study is expected to add evidence on the effectiveness and cost-effectiveness of an optimally facilitated, prepared and structured CMR in comparison with usual care in older patients presenting with a geriatric giant to their GP.

Geriatric giants are highly prevalent among older people and represent a major cause of impaired quality of life. Optimising the patient’s medication in addition to treating these geriatric problems or delaying their worsening by treatment, is expected to have a positive additional impact on the patient’s perceived health. Moreover, optimising drug use will also improve the effectiveness of drug treatment, prevent adverse drug reactions and potentially harmful drug interactions, and consequently hospital admissions or even death.

For healthcare professionals, handling DRPs in older people is a challenge. The burden of aging on the healthcare sector, care efficiency is an important issue.

The streamlining of the process, the experienced expert teams and minimising the contact moments with the patients due to the written questionnaire as proposed in this study increases the feasibility that CMRs can be implemented successfully in usual care. In practice, after this study, expert teams could be implemented in a GP cooperation or another regional care settings in which pharmacists and GPs should be trained and form expert groups.

The strength of this study is that it will be conducted in daily clinical practice and will resemble daily clinical practice as much as possible. This improves the possibilities to implement CMRs in the primary care setting.

The most important innovations compared to previous programs are:The CMR will not focus primarily on polypharmacy patients, instead the selection of older patients is based on episodes related to a geriatric giant;The CMR is prepared by a trained expert team consisting of an external GP and an external pharmacist who formulate a pharmacotherapeutic treatment plan for the patient’s GP;The coordination of the CMR at the primary care level is performed by a case manager, usually the practice nurse or assistant;The number of contacts with the patient is reduced by assessing the patient’s perspective by a written questionnaire instead of a home visit.

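### The stated recording of intervention costs omits the research assistant who helps prepare each medication review; followed as written, it understates incremental cost

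*Protocol article*

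**What the plan says.** Secondary outcome measures sets the perspective: "Costs will be measured from a societal perspective". The intervention cost is built from resource use: "information will be recorded by the expert team, the GP, the pharmacist and the practice nurse in terms of time and material spent", and the activities covered are those spent "on performing the CMR and the monitoring of the patients". The same section openly excludes one cost item, lost productivity, because nearly all patients will be retired.

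Under Intervention, Preparatory steps, the file for each review is put together before the expert team sees it: "The research assistant prepares together with the practice nurse the CMRs for the expert teams". The file draws on the GP record, the pharmacy and the screening questionnaire. It covers current drugs, dispensing history, possible drug related problems, medical problems, laboratory results and other measurements.

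Process analysis also registers how much time professionals spend on protocol activities, using structured forms, and plans interviews with practice nurses, GPs and expert-team members. Economic evaluation then turns costs and effects into ICERs, cost-effectiveness planes, acceptability curves and net monetary benefits.

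**The concern.** The list of people who record time does not match the list of people who deliver the intervention. Two workers prepare the reviews, the practice nurse and the research assistant, and only the nurse is a listed recorder. The expert team works from the prepared file, so someone would have to assemble it in routine care too. It is a per-review input and not a start-up cost.

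What is at stake is the economic conclusion. The Background names time investment as an obstacle to medication reviews, and the Discussion says that a cost-effective result would support nationwide implementation. An uncounted input that exists in one arm only does not cancel in the comparison. This is also a matter of prospective data collection: if the time is not recorded as reviews take place, a later analysis plan can estimate it but cannot retrieve it.

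**Working it through.** The article states no staff hours, unit costs or programme cost, so there is no figure to reproduce. The check sets the sections side by side and then derives the direction of the effect.

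**1. Who does the work and who records it**

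| Component (section) | Done by | Listed as recording time? |
|---|---|---|
| Preparing the review file (Preparatory steps) | Practice nurse | Yes |
| Preparing the review file (Preparatory steps) | Research assistant | No |
| The review itself (Clinical medication review by expert team) | External GP and pharmacist | Yes |
| Consultation on the treatment plan (Implementing the pharmacotherapeutic treatment plan) | Patient's GP | Yes |
| Six-month check (Monitoring the medication use) | Researchers | No |

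Two rows lack a recorder, and they differ in kind. The last row reads "Six months after inclusion a check will be carried out by the researchers". Its comparison with baseline drug use takes in all participating patients, so it is at least partly a research activity in both arms and not clearly an intervention cost. The research assistant's row is placed under Intervention and feeds reviews that only intervention patients receive.

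**2. Whether another section fills the gap**

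- Process analysis refers to professionals in general and does not name the research assistant. Its interviews cover nurses, GPs and expert-team members only.
- The Discussion gives coordination in primary care to a case manager, as a rule a practice nurse or assistant. That indicates who might do the work in practice. It does not say that the research assistant's time is recorded in the trial.
- The nurse's own entries cover the nurse's share of the preparation, not the assistant's.

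No section supplies the missing time.

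**3. Direction of the effect**

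Let ΔC be the true difference in mean cost (intervention minus control), ΔE the difference in mean effect, λ the ceiling ratio, and a > 0 the mean uncounted preparation cost per intervention patient. The control arm has no review to prepare, so its uncounted amount is 0.

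- Incremental cost as measured: ΔC − a, too low by a.
- ICER as measured: (ΔC − a)/ΔE, too low by a/ΔE when ΔE > 0.
- Net monetary benefit as measured: λΔE − (ΔC − a) = (λΔE − ΔC) + a, too high by a at every λ, whatever the sign of ΔE.
- Acceptability curve: the probability that net monetary benefit is positive. Adding a positive amount cannot lower it at any λ.

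**4. Size**

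The value of a is the assistant's minutes of true review preparation per patient multiplied by a wage rate. The article gives neither, so a cannot be computed.

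**The case against.** The strongest reply is that the article says who records time and does not give a closed list of cost items. It names one exclusion, lost productivity, and does not name this one. A condensed article may leave detailed costing to a fuller plan. Preparation is shared with the nurse, who is listed. Some of the assistant's work may serve the trial: both arms complete the screening questionnaire, and medical-record, laboratory and dispensing data are also collected as trial data.

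Part of this stands. The nurse's share is covered, and trial data collection should not be charged to the programme, so not all of the assistant's time is a missing intervention cost. The point about condensation carries less weight here, because the article does state its source of intervention costs and that statement does not fit its own delivery model.

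Two stronger readings are tempting and are not supported.

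- **Training is wrongly left out.** A reader might infer this, because the Training section sits under Intervention and says "Expert teams will follow accredited online courses for medication reviews and pharmacology in elderly and two medication review workshops", while the Discussion says that for later use "pharmacists and GPs should be trained and form expert groups". But the article is only silent on costing training; it does not exclude it. Whether training is treated as one-off, spread over time or left out is commonly settled in a full economic plan. For practice staff, who "will be instructed how to carry out the study protocol and will receive a handbook", the training is at least partly trial instruction.
- **A large share of the programme's cost is missing.** A reader might set an assumed preparation time against the review times in the Background, 15 to 60 minutes for a physician and 30 to 120 for a pharmacist, together 45 to 180. Assuming 15 to 60 minutes of assistant time gives 15/(180 + 15) = 8% up to 60/(45 + 60) = 57%. A range that wide is not evidence of size. The numerator is assumed. The denominator is a general figure for reviews, not this trial's recorded time, and includes no nurse time. Minutes are not costs, and the ICER rests on total costs, which also include healthcare, informal care and medication.

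**Conclusion.** The concern holds in limited form. The recording of intervention costs, as stated, does not include the research assistant's share of preparing the reviews, although the article makes that work part of the intervention. Followed as written, incremental cost is understated, and all three economic summaries move in the programme's favour.

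The direction rests on two premises: that at least some of the assistant's preparation is true delivery and not trial data collection, and that this time is not captured by a route the article does not mention. The size is unknown and may be small. The consequence is confined to the economic evaluation, since costs are a secondary outcome and the primary analyses of quality of life and geriatric symptoms do not use them. The treatment of training is at most something to state, not an error.

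**What to change.** - Add the research assistant to those who record time, on the structured registration forms already planned for the process evaluation.
- Have the form separate review preparation from trial data collection, and count only the former in the intervention cost.
- Value the preparation time at the rate of the staff who would do it in routine care. The Discussion points to a case manager, usually a practice nurse or assistant.
- State in one sentence how training is treated, for example through a sensitivity analysis with and without it.

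The cost is one more entry on an existing form, the assistant's effort in filling it in, and a little analysis work. The downside is that the reported intervention cost becomes slightly less favourable. If reviews have already been prepared without this record, the time can only be estimated afterwards and should be reported as an assumption with a range.

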### Control condition

Eligible patients who are listed in a control practice will be identified and selected in exactly the same manner as in the intervention group. They will be asked to give informed consent and to fill in the same questionnaires at inclusion, baseline, 3 and 6 months. Patients in control practices receive usual care, which means that no structured attention will be paid to their medication.

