### Economic evaluation

For the economic evaluation, missing cost and effect data will be imputed using multiple imputation according to the Multivariate Imputation by Chained Equations (MICE) algorithm developed by van Buuren using predictive mean matching and fully conditional specification [55]. The number of imputed datasets will be increased until the fraction of missing information is below 5% [56]. The imputed datasets will be analysed separately as described below and subsequently pooled using Rubin’s rules.

The effect measures that will be taken into account in the cost-effectiveness are QALYs, and changes in the VAS scores of the geriatric giant symptoms. For effects and costs, linear multilevel regression models will be estimated. Clustering at the level of GP practice will be included in these multilevel models. Incremental cost-effectiveness ratios (ICERs) will be calculated by dividing the difference in mean total costs between the treatment and control groups by the difference in mean effects between the groups. Costs generally have a highly skewed distribution; therefore, bootstrapping with 5,000 replications will be used to estimate bias-corrected and accelerated confidence intervals around cost differences [57]. To account for the clustering of data, bootstrap replications will be stratified for practice [58]. The uncertainty surrounding the ICERs which will be graphically presented on cost-effectiveness planes. Cost-effectiveness acceptability curves and net monetary benefits will also be calculated. Cost-effectiveness acceptability curves show the probability that the medication review programme is cost-effective in comparison with usual care for a range of different ceiling ratios thereby showing decision uncertainty.

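### Care use is first measured at 3 months, so non-drug costs have no pre-inclusion value and the cost comparison forgoes precision and direct protection against imbalance

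*Protocol article*

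**What the plan says.** All references are to the protocol article.

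- **Cost data.** Secondary outcome measures sets the timing of the "questionnaire on care consumption, including informal care after 3 months (t = 1) and after 6 months". No baseline administration is named, and month 3 carries the label t = 1. Prescribed-drug data come from the pharmacy's administration system instead.
- **Other outcomes.** The general schedule in Outcome measures is "Measurements by means of patient questionnaires and proxy assessments will be carried out at baseline, after 3 and 6 months". In Secondary outcome measures, medication satisfaction is recorded "with a written response assessed on a seven point Likert like scale at baseline, 3 and 6 months", and drug-related problems and self-reported adherence also have a baseline. Primary outcome measures gives quality of life and geriatric symptoms one too.
- **Records.** Outcome measures states: "Characteristics of medication, changes in medication and adherence to medication will be assessed using dispensing data from the patient’s pharmacist". It also takes morbidity from GP records. Monitoring the medication use has medication at 6 months "compared to baseline drug use of all participating patients". The eligibility search looks back 12 months in GP records, and Control condition applies the same identification to control practices.
- **Cost model.** Economic evaluation states: "For effects and costs, linear multilevel regression models will be estimated". Clustering by practice is included and no covariate is named.
- **Allocation and recruitment.** Ten practices per arm are randomised in two strata of practice size, before any patient is recruited and without blinding of patients, GPs or practice nurses (Abstract; Randomisation). GPs then remove patients from 8-weekly lists, including those they judge unable to take part (Exclusion criteria). Consent comes after allocation (Inclusion procedure).

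**The concern.** A patient's past care use is usually a strong predictor of later cost, and it is the natural covariate in a cost model. Here the instrument that captures informal, home and hospital care starts only after the intervention period has begun, so those components cannot be adjusted directly for their own earlier level. An analysis plan written later cannot repair this for informal care, because data never collected cannot be entered in a model.

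Two things are at stake. First, with 20 practices the arms may differ by chance in prior use, and without adjustment that difference adds noise to the estimated cost difference. Second, GPs who know their arm screen the patient lists, and patients consent afterwards, so the arms could differ in frailty and care use through selection. Prior use would be the most direct way to see that and partly adjust for it. The economic result matters here: the Abstract makes cost-effectiveness part of the aim, and the Discussion ties national roll-out to it.

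**Working it through.** The plan states no figure for this point, so there is none to reproduce. The check has two parts.

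**1. Which cost components have a pre-inclusion source?**

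| Component | Follow-up source | Pre-inclusion source in the article |
|---|---|---|
| Prescribed drugs | Pharmacy system | Within reach: dispensing data, baseline drug use |
| GP contacts, referrals | Care-consumption questionnaire | Within reach: GP records, already searched 12 months back |
| Home, hospital and other care | Care-consumption questionnaire | None by questionnaire; referrals in GP records cover part of hospital care |
| Informal care | Care-consumption questionnaire | None |

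The gap is real for the lower two rows. For the upper two the data are obtainable but not assigned to the cost model.

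**2. How large is the effect?** The article gives no cost SD, intraclass correlation (ICC) or correlation between periods. All three are assumptions, shown as ranges.

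*Chance difference in prior cost, in patient-SD units.* With 10 practices per arm and 25 patients per practice (500/20):

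SD of difference = √[(2/10) × (ICC + (1 − ICC)/25)]

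| Assumed ICC | SD of difference | Chance that it exceeds 0.2 SD |
|---|---|---|
| 0.005 | 0.095 | 3% |
| 0.02 | 0.109 | 7% |
| 0.05 | 0.133 | 13% |
| 0.10 | 0.165 | 23% |

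*Precision gained by adjustment.* With correlation r between prior and follow-up cost, taken as equal at patient and practice level, the standard error is multiplied by √(1 − r²):

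- r = 0.4: √(1 − 0.16) = 0.92, a cut of about 8%.
- r = 0.5: √(1 − 0.25) = 0.87, a cut of about 13%.
- r = 0.6: √(1 − 0.36) = 0.80, a cut of 20%.

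*Illustration in euro.* With 225 analysed per arm (22.5 per practice), SE = SD × √[(2/225) × (1 + 21.5 × ICC)].

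- SD 4,000, ICC 0: 4,000 × √0.00889 = 377.
- SD 8,000, ICC 0.05: 8,000 × √(0.00889 × 2.075) = 1,086.

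A carry-over slope of 0.4 applied to the first gives 151, and 0.6 applied to the second gives 652. So one SE of chance imbalance would contribute about 150 to 650 euro to the follow-up difference.

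*Is that extra error?* No. If SD and ICC are the same in both periods, the slope equals r and the carried-over part is one component of the unadjusted SE. In the larger case, √[652² + (0.80 × 1,086)²] = √[652² + 869²] ≈ 1,086, which is the SE already computed. Adjustment removes the 652 component and leaves about 869.

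**The case against.** A reader might infer that the cost comparison cannot be corrected at all for existing differences in healthcare use. The article does not support that. Dispensing data and GP records can supply earlier drug costs and GP contacts in both arms. Medication count and multi-morbidity, named as adjusters in Statistical analyses, are partial proxies. Economic evaluation does not exclude covariates, and their choice is commonly left to an analysis plan, so the lack of a named covariate is not an error in itself.

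A reader might also infer that a starting imbalance biases the cost result. Chance imbalance between randomised practices does not do so in expectation. It is sampling error, which the multilevel model and bootstrap intervals are meant to express. The euro figures are therefore not an addition to the reported uncertainty, and they rest wholly on assumed inputs. The article also gives no cost of a review against which to compare them.

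It can further be said that the general schedule, or the control arm's obligation to "fill in the same questionnaires at inclusion, baseline, 3 and 6 months", might cover care consumption at baseline. The specific sentence on the instrument names only months 3 and 6, and that is the text a study team would follow.

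Finally, respondents are older people with geriatric symptoms, some of whom need help with forms, so extra items carry a burden. That is fair, and it favours the records-based part of the remedy. What stands after all this is the stated schedule. It leaves non-drug care without a pre-inclusion measurement, and for informal care no later analysis decision can supply one. The randomisation argument also does not cover selection after open allocation.

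**Conclusion.** The point holds as a limited, inexpensive improvement to the economic evaluation. As scheduled, non-drug costs have no pre-inclusion value and no prior-use covariate is named. The cost comparison therefore loses precision and lacks a direct safeguard against imbalance or selective recruitment. Assuming r of 0.4 to 0.6, adjustment would reduce the SE by about 8% to 20%. That range applies to a prior-cost measure reaching such a correlation with total cost; records alone, without informal care, may fall short of it. Nothing in the article shows that selective recruitment will occur or how large it would be, and adjustment would remove it only so far as prior use captures it. The primary outcomes are not affected.

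**What to change.** 1. **Records, both arms, all patients including those already enrolled.** Extract dispensed-drug costs for the 6 months before inclusion from the pharmacy records, and GP contacts and referrals for the same period from the GP records. This lengthens the extraction window in sources already used and adds no patient burden.
2. **Cost model.** Name this pre-inclusion cost as a covariate in the multilevel cost model of the Economic evaluation section.
3. **Baseline questionnaire, patients still to be enrolled.** Add the care-consumption items, informal care included, with a 3-month recall to match the spacing of the later questionnaires. The cost is a somewhat longer baseline questionnaire.
4. **Stated limit.** Records cannot recover prior informal care for patients already enrolled. The economic report should say so.
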